**Fig. 3 jad-95-jad230241-g003:**
[figure not shown]
Target volumes for LDRT include the whole brain up to the C2 level to sufficiently cover the base of the skull.

### Follow-up (Visits 9–11)

All participants will visit the hospital approximately 1, 6, and 12 months after LDRT (visits 9, 10, and 11) to evaluate efficacy and safety. The examinations to be performed during the follow-up period are described in the Clinical Trial Schedule (Table 2).

**Table 2 jad-95-jad230241-t002:** Overall clinical trial schedule and detailed examination tests for the participants

	Screening	Baseline	Intervention/Treatment						Follow-up		
Visit	V1	V2	V3	V4	V5	V6	V7	V8	V9	V10	V11
Week(s)	–3 w ∼ –1w	–1w	1w	1w	2w	2w	3w	3w	7w	27w	51w
Day(s)	–21 ∼ –1	–7 ∼ –1	1	5±3d	8±3d	12±3d	15±3d	19±3d	49±7d	189±7d	357±7d
Informed consent	•									
Basic information	•									
^Underlyingdisease^	•									
Premedication	•									
Vital sign	•	•	•	•	•	•	•	•	•	•	•
Neurological examinations	•	•	•	•	•	•	•	•	•	•	•
Laboratory tests^1^	•									•	•
serum amyloid-β & tau protein	•										•
Amyloid PET	•									•	•
*APOE* genotyping	•									
serum cytokines^2^	•									•	•
K-MMSE-2	•									•	•
CDR	•									•	•
ADAS-K	•									•	•
CGA-NPI	•									•	•
K-iADL	•									•	•
Brain MRI	•									•	•
Low-dose radiation therapy			•	•	•	•	•	•		
Randomization		•								
Assessment of adverse event			•	•	•	•	•	•	•	•	•

^1^Laboratory tests include complete blood cell count, blood chemistry examination, electrolytes, thyroid hormone test. ^2^Serum cytokines include Interleukin-1 [IL-1], tumor necrosis factor-α [TNF-α], IL-10, transforming growth factor-β. PET, positron emission tomography; *APOE*, apolipoprotein; K-MMSE, Korean-Mini-Mental Status Examination; CDR, Clinical Dementia Rating scale; ADAS-K, Alzheimer’s disease assessment scale-Korea; CGA-NPI, Caregiver Administered-Neuropsychiatric Inventory; K-iADL, Korean Instrumental Activities of Daily Living; MRI, magnetic resonance imaging.

### Outcome measures (primary and secondary endpoints)

The primary endpoint is the score change of ADAS-K (range 0–70, higher scores indicate a worse outcome) 6 months after baseline and the number of adverse events 6 months after baseline determined by the Radiation Therapy Oncology Group toxicity grading system. The amount of change will be evaluated as a valid response if it shows an improvement of≥5% from the baseline score.

The secondary endpoints include the score change of K-MMSE-2 (range 0–30, higher scores mean a better outcome), CDR (range 0–3, higher scores mean a worse outcome), CGI-NPI (range 0–144, higher scores mean a worse outcome), and K-iADL (range 10–33, higher scores mean a worse outcome) after 6, 12 months from baseline. Also, we will additionally assess the primary endpoint 12 months after baseline. Changes in the SUVR of amyloid PET scans in the frontal, parietal, lateral temporal lobe, anterior wedge, and posterior gyri will be evaluated. The evaluation of the valid response is the same as that of the primary endpoint.

Furthermore, the primary endpoint evaluation will be analyzed by three institutions, and an additional analysis will be conducted to determine whether there are any differences among institutions.

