As for the twice weekly regimen rather than a daily RT, it was related to the LDRT as a treatment for osteoarthritis (OA). Several studies have demonstrated the efficacy of LDRT in modulating immune function, and it is used in European countries to relieve the symptoms of uncontrollable OA [26–28]. The most common regimen is to perform LDRT two to three times a week [28]. The interfraction interval is based on research by Moon et al. [29]. After hippocampal dentata gyrus (DG) was irradiated with LDRT, the number of Ki-67-positive and doublecortin-positive cells in DG declined sharply between 0 and 24-h post-irradiation, which then increased gradually to the sham RT level between 3 and 14 days of post-irradiation. Therefore, we tried to set the interval between twice-weekly treatments to no more than 3 days. Given the pilot clinical study by Cuttler et al. in which four AD patients were treated with LDRT at two-week intervals each using a CT scanner [15], it is reasonable to widen the RT interval. Furthermore, given the biology of normal neurons in response to radiation, it is likely that spacing the treatments is more favorable for repopulation than daily treatments [16].

Meanwhile, in the efficacy analysis, an improvement of≥5% will be evaluated as an effective response. To date, as the clinical trials on the effects of LDRT on patients with AD are ongoing or partially understood, a decision must be made after consultation with a neurologist. In the case of existing AD medication, the improvement in neurological function is almost 0%, and it only slows the rate of cognitive deterioration [30]. Therefore, LDRT was conservatively estimated to have a therapeutic effect, even with only a 5% improvement.

In conclusion, this trial will provide notable evidence on the efficacy and safety of LDRT as a new treatment strategy for AD.

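### The 5%-of-baseline response rule is a liberal criterion of efficacy, described as conservative, and one percentage has no common meaning across the trial's scales

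*Protocol article*

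**What the plan says.** In Outcome measures, the efficacy part of the primary endpoint is a change in score: "The primary endpoint is the score change of ADAS-K (range 0–70, higher scores indicate a worse outcome) 6 months after baseline". The count of adverse events is named beside it. The section then adds a threshold: "The amount of change will be evaluated as a valid response if it shows an improvement of≥5% from the baseline score".

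The next paragraph lists the secondary outcomes with their ranges: K-MMSE-2 (0-30, higher is better), CDR (0-3), the NPI (0-144) and K-iADL (10-33), the last three with higher meaning worse. It then adds the SUVR of the amyloid PET and closes with "The evaluation of the valid response is the same as that of the primary endpoint".

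The Discussion assigns the threshold to the efficacy analysis. Its reason is that existing AD drugs slow decline but produce almost no improvement, and it concludes that "LDRT was conservatively estimated to have a therapeutic effect, even with only a 5% improvement". It also says that the decision needs a neurologist's input.

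Statistical analysis names one kind of efficacy test: a paired t-test or signed-rank test of the 6-month change in each group. It names no test of response rates, and the sample size is not derived from any.

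**The concern.** The 5% rule is the only success criterion that the article states, and its justification runs the wrong way. Conservative should mean hard to pass, but a low threshold makes it easy to declare an effect. The reasoning also moves from an average to individuals: a drug with a mean improvement near zero still leaves many patients above and many below their baseline.

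The second problem is scope. A percentage of baseline is comparable across scales only if each has a meaningful zero and fine enough steps. These scales do not.

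At stake is how the result is read. If a share of responders is reported for each LDRT arm, or an arm is said to have achieved a valid response, part of that reflects ordinary variation in scores. The sham arm corrects for this only if its response is subtracted, and the efficacy test named in the article works within each arm.

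**Working it through.** The article gives no expected response rate, so there is no stated figure to reproduce. It also gives no baseline mean, SD of change or retest error for any scale. Items 1 to 3 therefore rest on assumed inputs. Item 4 uses the stated ranges, with step sizes assumed where marked.

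**1. Per-patient reading, ADAS-K.** Let B be the baseline score, m the mean sham worsening in points over 6 months, and s the SD of the change. Response requires a fall of at least 0.05 × B. With normally distributed change:

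P(response) = Φ((−0.05 × B − m) / s)

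The bar is 0.75 points at B = 15, 1.0 at B = 20 and 1.5 at B = 30, on a 70-point scale.

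Worked case, B = 20, m = 1, s = 5: Φ((−1 − 1)/5) = Φ(−0.40) = 34%. With m = 0: Φ(−0.20) = 42%.

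Results for B = 20:

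| m | s = 3 | s = 4 | s = 5 | s = 6 | s = 7 |
|---|---|---|---|---|---|
| 0 | 37% | 40% | 42% | 43% | 44% |
| 1 | 25% | 31% | 34% | 37% | 39% |
| 3 | 9% | 16% | 21% | 25% | 28% |

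Over B = 15, 20, 25, 30; m = 0, 1, 1.5, 2, 3; and s = 3 to 7 (100 combinations):
- lowest: B = 30, m = 3, s = 3, Φ(−4.5/3) = Φ(−1.5) = 7%
- highest: B = 15, m = 0, s = 7, Φ(−0.75/7) = 46%
- median: 30%

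Among 20 sham patients that is about 1 to 9 responders (20 × 0.07 = 1.4; 20 × 0.46 = 9.2), centrally 6 (20 × 0.30).

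**2. The Discussion's own premise.** Take its near-zero average as exactly zero and express the SD as a percentage of baseline. Then P = Φ(−5 / SD%):
- SD 3%: 5%
- SD 5%: 16%
- SD 10%: 31%
- SD 20%: 40%

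Individual 5% gains become rare only if the SD of change is about 3% of baseline, or 0.6 points at B = 20. A near-zero mean does not imply that.

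**3. Group-mean reading.** If the rule applies to an arm's mean (n = 20, B = 20, s = 5), the standard error is 5/√20 = 1.12.
- No true change: Φ(−1/1.12) = 19%
- True worsening of 1 point: Φ(−2/1.12) = 4%

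The two readings give very different answers, and the text does not choose between them.

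**4. The other scales.** Whole-point scoring is assumed for the NPI and K-MMSE-2, and half-point steps for CDR at these levels.
- CDR: at a baseline of 0.5 or 1, the bar is 0.025 or 0.05. The smallest improvement, 0.5, is 100% or 50% of baseline. Any step passes, so 5% does not act as a cut.
- NPI: at a baseline of 0 the percentage is undefined. At 1 to 20 the bar is 0.05 to 1.0, so one point suffices.
- K-iADL: the best possible score is 10, so the percentage is taken of a number containing a 10-point offset. A patient at 15 is 5 points from the best score and needs 0.75, or 15% of that distance. A patient at 30 is 20 points away and needs 1.5, or 7.5%.
- K-MMSE-2: 5% of 13 to 20 is 0.65 to 1.0, so 1 point. 5% of 21 to 24 is 1.05 to 1.2, so 2 points.

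**The case against.** The strongest reply is that the rule does little formal work. The endpoints are score changes, the named tests are tests of change, and no responder test or response-based sample size appears. The trial is called exploratory. It has a sham arm to expose placebo response, and the Discussion states the intention to compare with it. All of this stands. A reader might infer that dichotomising throws away the primary data, or that no comparison with sham will be made. The article supports neither: the scores remain analysable as change, and a between-arm analysis may be set out in the full protocol or analysis plan.

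A reader might also infer that 5% lies within measurement error, or that about a third of sham patients will respond by chance. Neither can be derived from the article. A third is a reasonable central value under assumed inputs, but the range is 7-46%, and on the group-mean reading the figure does not apply. For SUVR the article gives no basis for calling 5% noise.

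Three further limits stand:
- Entry requires K-MMSE 13-24 or CDR 0.5 or 1, so neither baseline range is guaranteed for every patient.
- A patient at NPI 0 or K-iADL 10 could not improve under an absolute cut either. Floor patients are not a defect peculiar to a percentage rule.
- The sentence extending the rule follows the SUVR sentence and could be read as covering SUVR alone, though all secondary outcomes is the natural reading.

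The reply does not rescue the rule as a criterion. The Discussion places it in the efficacy analysis, and the article offers no other standard of success.

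**Conclusion.** The concern holds for the rule's use as a criterion of efficacy. Calling it conservative is wrong in direction, and the supporting argument confuses a mean with individual change. Its failure to carry one meaning across CDR, NPI, K-iADL and K-MMSE-2 follows from the stated ranges and the assumed scoring steps.

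The size on ADAS-K rests on assumptions: about 30% of sham patients centrally and 7-46% over the grid if read per patient; 19% (no true change) or 4% (1 point of worsening) for an arm of 20 if read as a group mean. The damage is to how efficacy is declared, chiefly if response is read within an arm without subtracting the sham response. The score-change data are not affected.

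**What to change.** 1. In Outcome measures, remove the 5% rule as a criterion of efficacy for the primary and secondary outcomes. In the Discussion, delete the word conservatively and the argument from a near-zero average.
2. State that efficacy is judged by the baseline-adjusted mean difference from sham in 6-month ADAS-K change, for each LDRT arm, with its confidence interval. Judge the secondary scores and SUVR by change versus sham.
3. If a responder display is kept, label it supportive and say that it is per patient. Fix a cut for each scale with the neurologists before unblinding, and report the difference in proportions from sham. Say how patients already at the best score are handled, since no cut lets them respond.

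The cost is wording and a little programming, with no new data. The downside is losing a simple per-patient label.

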### Recruitment and eligibility criteria

This trial is conducted jointly by three institutions: Kyung Hee University Hospital in Gangdong, Chungbuk National University Hospital, and SMG-SNU Boramae Medical Center. Among the patients with AD who visit the Department of Neurology of each institution, those who meet the inclusion criteria for this study are referred to the Department of Radiation Oncology. In addition, with content approved by the Institutional Review Board (IRB), we are promoting patient recruitment through in-hospital publicity and advertisements in newspapers and subways.

The inclusion and exclusion criteria are presented in Table 1. All the following criteria should be satisfied for the patients to be included in the study: 1) age between 60 and 85 years; 2) diagnosed with probable AD dementia based on the new diagnostic criteria for AD outlined by the National Institute on Aging and Alzheimer’s Association; 3) stable maintenance of general AD drug treatment (donepezil, galantamine, rivastigmine, or memantine) for more than 3 months; 4) amyloid accumulation in the brain confirmed by amyloid positron emission tomography (PET); 5) mild AD (score range of 13 to 24 on the Korean Mini-Mental State Examination [K-MMSE] or 0.5 or 1 on the Clinical Dementia Rating scale [CDR]); 6) ability to perform cognitive function tests and imaging tests without help of others; and 7) accompanied by a guardian who provides information on the patient’s overall status, cognitive function, and functional changes. Patients who meet any of the exclusion criteria will be excluded from the study. The major exclusion criteria are 1) previous history of radiation to the brain; 2) previous history of malignancy diagnosed within 5 years from the time of screening or currently being treated; 3) cognitive decline associated with drugs or neurological or neurodegenerative conditions, not AD; and 4) clinically significant and unstable mental illness. The exclusion criteria are presented in Table 1.

**Table 1 jad-95-jad230241-t001:** The inclusion and exclusion criteria for the clinical trial

Inclusion	Exclusion
Aged between 60 and 85 years	Previous history of radiation to the brain
Diagnosed with AD dementia based on the new diagnostic criteria for Alzheimer’s disease outlined by the National Institute on Aging and Alzheimer’s Association	History of seizure within the previous 10 years of the screening time

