### Sample size calculation

This trial is intended to further evaluate the treatment effect of LDRT on AD, and it is difficult to calculate the appropriate effect size for the treatment and control groups. Therefore, the purpose of this study is exploratory, in the form of a pilot study to compare efficacy. Bonferroni correction will be performed, and a comparative, parallel, three-arm design will be adopted with 80% power and a 2-sided alpha of 0.05. Finally, 20 people per group, for a total of 60 people, is calculated as the number of samples considering the dropout rate.

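### The CDR secondary outcome is change on the 0–3 global score in patients targeted at 0.5 or 1: too coarse for the 5% response rule and insensitive with 20 per arm; the sum of boxes would be a finer outcome

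*Protocol article*

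**What the plan says.** All references are to the protocol article.

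- **Outcome measures (primary and secondary endpoints).** The secondary list includes score change in "CDR (range 0–3, higher scores mean a worse outcome", assessed "after 6, 12 months from baseline". No finer CDR score is named here or anywhere else in the article.
- **Same section, response rule.** For the primary endpoint: "The amount of change will be evaluated as a valid response if it shows an improvement of≥5% from the baseline score". The paragraph on secondary endpoints closes with: "The evaluation of the valid response is the same as that of the primary endpoint". That sentence follows the one on amyloid PET uptake. Its natural reading covers all the secondary scores, CDR included, but the text does not say so expressly.
- **Recruitment and eligibility criteria, and Table 1.** The target is "mild AD (score range of 13 to 24 on the Korean Mini-Mental State Examination [K-MMSE] or 0.5 or 1 on the Clinical Dementia Rating scale". The two scales are joined by an 'or', so a patient who qualifies on K-MMSE could enter at another CDR level.
- **Table 2.** CDR is scheduled at V1, V10 and V11.
- **Sample size calculation.** There are 20 patients per group and 60 in total, and the study calls itself exploratory: "Bonferroni correction will be performed, and a comparative, parallel, three-arm design will be adopted with 80% power and a 2-sided alpha of 0.05".
- **Discussion.** Of existing drug treatment the authors write that "it only slows the rate of cognitive deterioration". No rate of CDR stage change is given.

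**The concern.** By stating the range 0–3 the article selects the scale; this is not a detail left for a later document. A patient who enters at 0.5 or 1 cannot register a small change on it. The score either stays where it is or moves by a whole stage.

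This has two consequences. First, a percentage threshold meant to separate small real improvement from none does no such work on CDR. Second, with 20 patients per arm, graded change is reduced to a handful of stage moves, so an unchanged CDR would say little about whether LDRT slowed decline. CDR is the only global staging measure among the outcomes, so a flat result could be misread as evidence of no clinical effect.

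**Working it through.** **Inputs from the article.** CDR range 0–3; target entry levels 0.5 and 1; response threshold 5%; 20 per arm; two-sided alpha 0.05 with a Bonferroni correction whose number of comparisons is not stated. I show 0.05, and 0.025 as the value for two comparisons.

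**Input assumed.** The share of sham patients who worsen by one stage: 10–40%. The article gives no such figure.

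**No planned figure to reproduce.** No power or sample-size figure is given for CDR. The overall 20 per group comes without an effect size, SD or dropout rate, so it can be neither confirmed nor refuted.

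**1. Response rule against step size.** The smallest improvement from either target level is 0.5.

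| Baseline | 5% of baseline | Smallest improvement | As % of baseline | Multiple of threshold |
|---|---|---|---|---|
| 0.5 | 0.025 | 0.5 | 0.5/0.5 = 100% | 20 |
| 1 | 0.05 | 0.5 | 0.5/1 = 50% | 10 |

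On CDR the rule therefore means only 'improved by at least one stage'. Any threshold up to 50% would classify these patients identically. This step needs no assumption about rates of progression.

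**2. How many stage moves are needed.** Fisher's exact test, two-sided, 20 versus 20, with *x* movers in one arm and none in the other: p = 2·C(20,x)/C(40,x).

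- x = 4: 2 × 4845/91390 = 0.106
- x = 5: 2 × 15504/658008 = 0.047
- x = 6: p = 0.020

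So 5 versus 0 is needed at 0.05, and 6 versus 0 at 0.025.

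**3. Power for worsening by one stage.** With no movers in the LDRT arm, power at 0.05 is P(X ≥ 5) and at 0.025 is P(X ≥ 6), where X is binomial with n = 20 and the sham rate. The halved-rate columns sum over all outcome pairs that reach significance.

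| Sham rate | LDRT 0%, alpha 0.05 | LDRT 0%, alpha 0.025 | LDRT halves rate, alpha 0.05 | LDRT halves rate, alpha 0.025 |
|---|---|---|---|---|
| 10% | 4% | 1% | 2% | 0.4% |
| 20% | 37% | 20% | 7% | 3% |
| 30% | 76% | 58% | 12% | 7% |
| 40% | 95% | 87% | 19% | 12% |

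**4. The within-group test that the article names.** An exact signed-rank test with zeros dropped, and k movers all in one direction, gives p = 2 × 0.5^k. Five movers give 0.0625 and six give 0.031, so at least six of 20 must move the same way.

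**5. What cannot be computed.** The article gives no SD or expected change for the sum of boxes, so its power cannot be stated. For any continuous score with 20 analysed per arm, 80% power needs a standardised difference of (1.960 + 0.842) × √(2/20) = 0.89 at alpha 0.05, 0.98 for two comparisons and 1.02 for three.

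**The case against.** The strongest reply is that the Fisher calculation studies a different endpoint. The article specifies a signed score change and names paired tests, and the trial looks for improvement as well as slower decline. If some LDRT patients improve by one step while some sham patients worsen, the evidence builds faster. With 20 per arm, everyone else unchanged and an exact two-sided permutation test on mean change:

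- 4 sham worsen, 2 LDRT improve: p = 0.032
- 3 worsen, 3 improve: p = 0.034
- 4 worsen, 4 improve: p = 0.009
- 2 worsen, 2 improve: p = 0.13

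A two-sample t-test on 4 versus 0 movers also gives p of about 0.04, although it rests on four non-zero values. These figures are unadjusted and their rates are assumed, but they stand. A reader might infer from the Fisher figures that the global CDR cannot show an effect at all; that does not follow.

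Other parts of the reply also stand. A reader might take it as given that few patients will change stage within 6 to 12 months. The Discussion remark concerns what existing drugs do; it gives no speed of decline and does not mention CDR. A reader might also assume that every patient starts at 0.5 or 1, which the 'or' in the entry criterion does not guarantee. Graded change is already captured by ADAS-K, K-MMSE-2, K-iADL and the neuropsychiatric inventory, and CDR decides nothing in a self-described exploratory trial. At this sample size a null result on any scale is partly a matter of numbers.

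None of this rescues the 5% rule on CDR, and none of it gives a reason to prefer the coarser of two scores from the same instrument.

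**Conclusion.** The concern holds in a limited form. As fixed, the CDR outcome is a coarse staging score in a population aimed at two of its levels. The 5% response rule is uninformative on it, because the smallest improvement is 10 to 20 times the threshold. That conclusion rests on the article's own figures and on reading the response rule as covering all secondary scores.

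Low sensitivity rests on the assumed sham rates. Power is about 4–37% at 10–20% versus 0% and at most 19% if LDRT halves a rate of up to 40%. It is 76–95% at 30–40% versus 0%, and higher than the worsening-only figures if treated patients also improve. The supported statement is that an unchanged global CDR would be weak evidence either way, not that the outcome is bound to fail.

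That the CDR interview supplies item ratings which can be summed is a property of the instrument that the article does not state. The consequence is confined to one secondary outcome.

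**What to change.** In the outcome section, replace CDR on the 0–3 range with change in the CDR sum of boxes from V1 to V10 and V11, higher being worse. Keep the global CDR for eligibility and report it descriptively as a table of stage shifts by arm. State that the 5% response rule does not apply to the global CDR.

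No visit or procedure is added, since CDR is already scheduled at all three visits. There is a cost, however. The box scores must be entered in the trial database, and for patients already assessed (the abstract says recruitment is under way) they must be retrieved from source records. Any that cannot be recovered would leave gaps at baseline. The registered secondary outcome wording must also be amended, with a date and reason, before analysis.
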